# Dose-related effects of vitamin D on immune responses in patients with clinically isolated syndrome and healthy control participants: study protocol for an exploratory randomized double- blind placebo-controlled trial

**DOI:** 10.1186/1745-6215-14-272

**Published:** 2013-08-27

**Keywords:** Vitamin D, Clinically isolated syndrome, Multiple sclerosis, Immunomodulation, Cholecalciferol, Clinical trial

## Abstract

**Background:**

There is increasing evidence linking vitamin D deficiency to both susceptibility to, and severity of, multiple sclerosis (MS). Patients with the clinically isolated syndrome represent the initial presentation of a demyelinating disorder, and those with asymptomatic lesions on magnetic resonance imaging (MRI) are at risk of progression to clinically definite MS. The aims of this study are to examine the immunologic effects of vitamin D in both healthy individuals and in patients with clinically isolated syndrome, and in the latter group the effects on disease progression assessed by MRI and clinical measures.

**Methods/Design:**

This is a single-center double-blind randomized placebo-controlled clinical trial. The primary endpoint is the immunologic effects of two doses of vitamin D compared with placebo over 24 weeks in both healthy control participants and patients presenting with the clinically isolated syndrome. Healthy control participants (n = 39) and patients with clinically isolated syndrome (n = 45) will be randomized to one of three arms, namely 1) vitamin D 5,000 IU daily, 2) vitamin D 10,000 IU daily, or 3) placebo, and followed up for 24 weeks. In both patients and healthy control participants, the primary outcome will be immunologic measures of the frequency of CD4 T-cell subsets and cytokine responses in peripheral blood mononuclear cells, assessed at baseline, and after 16 and 24 weeks of treatment. Secondary endpoints, in the patients with clinically isolated syndrome, will be relapse activity, and the number of new T2 lesions and gadolinium-enhancing lesions assessed by MRI in the two vitamin D-treated groups compared with the placebo-treated group over the 24 weeks of the study.

**Trial registration:**

EU Clinical Trials Register: EudraCT: 2012-000635-68. ClinicalTrials.gov identifier: NCT01728922

## Background

Multiple sclerosis (MS), a chronic inflammatory disease of the central nervous system, is the most common disabling neurologic disorder of young adults. The causes of MS remain unknown, but it is widely believed that there is interplay between genetic and environmental factors [1]. Evidence for the role of the environment in the development of MS is supported by a strong correlation between MS incidence/prevalence and increased latitude and lower levels of sun exposure, suggesting an association with vitamin D production [2-4]. Individuals who emigrate before the age of 15 years from an area of high MS prevalence to one of low prevalence, acquire the lower risk of MS in their new country of residence. Migration studies provide perhaps the strongest support for the role of environmental factor(s) in this disease [5,6].

People living at high latitudes are generally deficient in vitamin D, as measured by serum 25-hydroxyvitamin D (25(OH)D) levels [7,8]. In one study, mean winter 25(OH)D levels in healthy control subjects in Ireland were 36.4 nmol/l, and more patients with MS had vitamin D deficiency (serum 25(OH)D levels less than 25 nmol/l) compared with control subjects [9]. Patients have lower serum vitamin D levels during MS relapses, and also have blunted parathyroid hormone responses [10,11]. In 267 Dutch patients with relapsing remitting multiple sclerosis (RRMS), higher vitamin D levels were associated with an increased chance of remaining relapse-free [11]. In 134 North American patients with RRMS or clinically isolated syndrome (CIS) of pediatric onset, the strongest predictor of further relapse was the baseline serum vitamin D level [12]. In a prospective Australian study of 145 patients with RRMS, each increase of 10 nmol/l in baseline serum vitamin D level was associated with a 12% reduction in the risk of a further relapse [13]. Vitamin D deficiency may increase susceptibility to MS even *in utero*; higher maternal vitamin D intake during pregnancy was associated with a 38% lower risk of MS in offspring [14], and maternal vitamin D levels greater than 75 nmol/l were associated with a 61% reduced risk of MS in children [15]. Month of birth studies showing an increased MS incidence in those with spring versus autumn births also provide evidence of the role of maternal vitamin D [16].

The potential therapeutic effect of vitamin D supplementation was first suggested by Goldberg in 1986 [17]. Dosing studies in healthy volunteers have shown that supplementation with vitamin D 10,000 IU daily results in an increase in serum 25(OH)D levels of 150 nmol/l over a 12 week period [18]. A Canadian phase I/II open-label, randomized, placebo-controlled trial (RCT) of 49 patients with RRMS who were randomized to placebo or escalating doses of vitamin D over a 52 week period showed a trend toward relapse reduction in the actively treated group [19]. This study was primarily aimed at establishing the safety and tolerability of high-dose vitamin D supplementation; the mean vitamin D dose was 14,000 IU per day, and there were no adverse events or hypercalcamia despite maximum mean vitamin D levels of 413 nmol/l being achieved. The results from this phase II trial [19], and from dosing [18] and observational studies [12,13], suggest that pharmacologic doses of vitamin D of up to 10,000 IU/day are safe, and may reduce the risk of relapse by a factor superior to the 30% reduction reported from the pivotal trials of interferons in RRMS [20,21].

Vitamin D modulates both the innate and adaptive immune systems [22]. The active metabolite, 1,25 (OH) vitamin D, primarily mediates its effects through the intracellular vitamin D receptor (VDR) [23], which is present in monocytes, dendritic cells, B-cells, and CD4+ T-cells [11,22]. Activation of VDR alters transcription, proliferation, and differentiation of immune cells [23], and modulates immune response both indirectly, by reducing the activation of pro-inflammatory T-cells by antigen-presenting cells [24], and directly, by inhibiting T-cell and B-cell proliferation [22,25]. This results in a T-helper (Th) 2-cell driven anti-inflammatory state [11,22,26].

There is thus accumulating evidence that vitamin D deficiency increases susceptibility to MS, and that vitamin D supplementation reduces disease activity by immunomodulatory mechanisms. It seems probable that serum vitamin D levels of greater than 100 nmol/l are required to produce the immunologic effects of vitamin D and thus, in patients with MS with vitamin D deficiency, doses of 5,000 to 10,000 IU/day are needed to achieve this. Most patients with RRMS, once diagnosed, commence treatment with first-line disease-modifying therapies (DMTs). Several RCTs are underway to examine the effects of vitamin D supplementation in patients with RRMS already receiving first-line DMTs, using clinical and MRI outcomes [27,28]. In the UK and Ireland, patients with CIS are not usually commenced on DMTs until there is clinical or MRI evidence of dissemination in time. These CIS patients, at risk of developing RRMS, may be recruited into trials of potentially therapeutic agents in order to examine the efficacy of specific therapies in preventing the development of clinically definite MS [29]. We have therefore designed this RCT to examine, over a 24 week treatment period the effects on immunologic measures as a primary outcome, both in patients with CIS and in healthy control participants, randomized to either of two doses of vitamin D (5,000 or 10,000 IU) or to placebo. In addition, in the patients with CIS, clinical and MRI efficacy measures will be assessed as secondary outcomes.

## Methods/Design

### Trial design

This is a single-center investigator-led, phase II, exploratory, double-blind, dose-ranging, randomized, placebo-controlled trial to assess the immune responses to two doses of vitamin D in patients with CIS and in healthy control participants. Recruitment commenced in November 2012. In total, 45 patients with CIS and 39 healthy control participants will be enrolled and randomized to one of three arms, placebo oil or vitamin D oil (Vigantol®; Merck Serono, Darmstadt, Germany) at a dose of 5,000 IU or 10,000 IU, all of which will be taken orally for a period of 24 weeks.

### Ethics

Ethical approval has been granted by St Vincent’s Hospital Ethics and Medical Research Committee, and the study has been approved by the Irish Medicines Board. The study will comply with the ethical principles as set down in the Declaration of Helsinki, and will be conducted in accordance with good clinical practice as defined by the International Conference on Harmonisation (ICH). The trial is registered with ClinicalTrials.gov NCT01728922 and EU Clinical Trials Register EudraCT number 2012-000635-68.

### Study participants

Study participants will be composed of two groups: 1) 45 patients with CIS, and 2) 39 healthy control participants.

#### Inclusion criteria

1) Patients with CIS aged between 18 and 55 years will be eligible for entry into the study if symptom onset occurred within 3 months of screening, they have two or more asymptomatic T2 lesions on MRI brain consistent with demyelination, not treated with steroids within 30 days of screening and are not on any other DMT.

2) Healthy control participants will be recruited from hospital staff, and will be aged between 20 and 40 years with a female:male ratio of 2:1, in line with the gender ratio seen with CIS.

#### Exclusion criteria

Exclusion criteria both for patients with CIS and for healthy control participants include: no history or evidence of hypercalcemia, renal impairment, vitamin D intolerance, parathyroid dysfunction, sarcoidosis, prior or current treatment with thiazide diuretics, or vitamin D supplementation of greater than 1,000 IU/day. Exclusion criteria for patients with CIS include: 1) if their symptoms might be explained by another diagnosis other than MS; 2) occurrence of an exacerbation less than 6 weeks prior to study entry; 3) previous treatment with β-interferons or glatiramer acetate in the 3 months before study entry, previous treatment with steroids in the 4 weeks before study entry, or any previous treatment with mitoxantrone or other immunosuppressant; and d) concurrent enrolment in any other clinical trial investigating DMT in CIS.

All female patients and healthy controls will be advised not to become pregnant for the duration of the study, and if sexually active to use effective contraception for the duration of the study and for 3 months after.

### Randomization

Patients with CIS and healthy control participants who fulfill the inclusion criteria will be enrolled in the study after providing informed consent at the screening visit. At the baseline visit, study participants who remain eligible will be assigned a number in ascending order: 1 to 45 for the CIS group and 1 to 39 for controls. The CIS group will be denoted by an X before this number, and the controls a Y. These numbers were randomized using the software program GraphPad [30] by the hospital pharmacist. The healthy control participants and patients with CIS will be randomized separately to maintain equal numbers in the three treatment arms of both these study groups.

### Interventions

#### Active therapy

The active therapy is vitamin D. The active principle will be cholecalciferol in the form of an oil (Vigantol Oil®; Merck Serono, Darmstadt, Germany), which is biologically inactive and is a precursor for the metabolically active metabolite calcitriol (1,25(OH)2D3).

#### Placebo therapy

A placebo oil, not containing vitamin D but identical to the active principle in all other respects, will be used.

#### Dispensing

Both the active and placebo oils will be dispensed in bottles with droppers, which contain 10 ml of fluid, with 20,000 IU of cholecalciferol per ml.

### Study endpoints

The primary endpoint is the effect of oral vitamin D at 5,000 and 10,000 IU/day compared with placebo on the frequency of CD4 T-cell subsets and cytokine responses in peripheral blood mononuclear cells in patients with CIS and in healthy control participants at weeks 16 and 24 compared with baseline.

Secondary endpoints include: the following. 1) In the patients with CIS having MRI brain scans at baseline and week 24, the number of new and enlarging T2 lesions and gadolinium-enhancing lesions at week 24 compared with baseline in patients receiving oral vitamin D at 5000 IU and 10,000 IU/ day compared with placebo, 2) In the patients with CIS, the effects of oral vitamin D at 5,000 and 10,000 IU/day compared with placebo on relapse occurrence, calculated as the annualized relapse rate (ARR), the percentage of patients who are relapse-free, and time to first relapse. 3) The effects of oral vitamin D at 5,000 and 10,000 IU/day compared with placebo on the percentage of treated patients with CIS who are free from any evidence of disease (clinical and MRI) activity.

### Study visits and outcome parameters

Participants will be screened following discussion of the trial and provision of signed, fully informed consent. If the participants satisfy the inclusion criteria at screening, they will then be scheduled for a baseline visit. The study scheme is outlined in Figure 1. There will be follow-up visits scheduled every 4 weeks visits until the end of study visit at week 24, and a safety visit at week 28 will also be arranged.

**Figure 1 F1:**
[figure not shown]
**Schematic diagram of study structure.** There are two study groups of subjects: 39 healthy control participants and 45 patients with clinically isolated syndrome (CIS). Each of the two groups will be randomly allocated to one of three blinded treatments: placebo, vitamin D 5,000 IU, or vitamin D 10,000 IU daily. Study duration is 24 weeks with immunologic testing (primary endpoint) of all study participants at baseline, week 16, and week 24. There will be 4-weekly clinic visits to assess safety measures and clinical status. 4 weeks after completion of the study there will be a follow-up safety visit. Magnetic resonance imaging will be carried out at baseline and week 24 in the CIS population only.

At all visits, study participants will have any changes in medical history or medications recorded, and will undergo a general physical and neurologic examination. Patients with CIS will be assessed for any evidence of relapse, defined as the appearance of a new neurologic abnormality or reappearance of a previously seen neurologic abnormality, separated by at least 30 days from the onset of the preceding event. The abnormality must be present for at least 24 hours, must be based on objective clinical evidence, and must occur in the absence of fever or known infection.

Blood biochemistry, including liver function tests, electrolytes, urea, creatinine, and serum calcium will be measured at all study visits.

Serum vitamin D levels and parathormone levels will be assessed at baseline, and at weeks 4, 8, 12, 16 and 24. Serum 25(OH)D levels will be measured by liquid chromatography-mass spectrometry. Intact parathormone levels will be measured by a two-step sandwich immunoassay using chemiluminescence technology.

Immunologic analysis will be carried out at baseline, and at weeks 16 and 24. Peripheral blood mononuclear cells (PBMCs) will be isolated within 12 hours of drawing blood, and cryopreserved until samples from all three time points have been collected. Cytokine production will be measured by ELISA, and will include 1) cytokine production by T cells and by other cells such as monocytes, and 2) flow cytometry, gating specifically on CD4 and CD8 T cells. 1) For analysis of PBMC cytokine production, PBMCs from each timepoint will be thawed out and stimulated with antigen (purified protein derivative (PPD) and tetanus toxoid) or polyclonal stimuli (anti-CD3 and phytohaemaglutinin). After 3 to 5 days (for polyclonal or antigen-specific stimulation respectively), the cell culture supernatants will be assayed by ELISA for cytokines including interleukin (IL)-10 and IL-17, and interferon (IFN)-γ. 1) For flow cytometry analysis of T-cell subsets, stimulated PBMCs from experiment 1, will be re-stimulated on day 5 with PMA and ionomycin in the presence of brefeldin A for 5 hours, followed by cell surface staining for T-cell markers (CD3, CD8) and intracellular staining for cytokines including IL-10, IL-17, and IFN-γ. The cells will be acquired on a FACSCanto II flow cytometer (Becton Dickinson), and analyzed using FlowJo software. Cytokine production by CD3+ CD8− (CD4 T-cells) and CD3+ CD8+ (CD8 T-cells) will be analyzed.

### *MRI scanning* at baseline visit and week 24

Brain MRI will be performed with contiguous axial 3 mm thick slices. Sequences will include axial and coronal T1-weighted spin echo (before and after gadolinium contrast enhancement), axial and sagittal PD/T2-weighted, and axial fast fluid attenuated inversion recovery, before contrast. MRI assessment will include 1) number of gadolinium enhancing lesions, 2) number of new and enlarging T2 lesions, and 3) the total number of new lesions (the sum of 1) and 2)).

An enhancing new T2 lesion will be considered a single lesion. Two radiologists will together examine the MRI scans at baseline and week 24, without having knowledge of the treatment group to which the patient/participant belongs. The two radiologists will determine by consensus for each study subject the numbers of new and enhancing T2 lesions at week 24 weeks compared with baseline, and thus the cumulative total number of new lesions over the 24 week period. Mean and median T2 and gadolinium enhancing lesions will be assessed for each treatment allocation group at baseline and 24 weeks.

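### The MRI total of new lesions still counts a lesion that enlarges and enhances twice, and the readers' sentence says enhancing where the endpoint says enlarging (minor)

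*Protocol article*

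**What the plan says.** Three places in the protocol article bear on the lesion count.

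- **Study endpoints**, first secondary endpoint: "the number of new and enlarging T2 lesions and gadolinium-enhancing lesions at week 24 compared with baseline", compared between each vitamin D dose and placebo. The third secondary endpoint is the percentage of CIS patients with no clinical or MRI disease activity.
- **MRI scanning at baseline visit and week 24**, assessment list: "MRI assessment will include 1) number of gadolinium enhancing lesions, 2) number of new and enlarging T2 lesions". The third item is "the total number of new lesions (the sum of 1) and 2".
- **Same section, reading rules**: "An enhancing new T2 lesion will be considered a single lesion". Two radiologists, blinded to treatment, then agree on "the numbers of new and enhancing T2 lesions at week 24 weeks compared with baseline". The running total for the study period is taken from what they agree.

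**The concern.** There are two separate problems.

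1. **Incomplete overlap rule.** A lesion can be on both lists that are summed. The single-lesion rule shows that the authors saw this and meant each lesion to count once, but it covers new T2 lesions only. The second list also contains enlarging T2 lesions, and nothing covers one of these that enhances.

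2. **A different word in the readers' sentence.** It pairs new with enhancing where the endpoint and the assessment list pair new with enlarging. It is also the sentence from which the cumulative total is said to follow. If a reading form were built from it literally, an enlarging lesion without enhancement would have no place on the form.

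The first problem can inflate the total. The second, if acted on, can lower the T2 count and could let a patient whose only activity is a non-enhancing enlarging lesion be classed as free of disease activity.

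**Working it through.** The plan gives no figure that depends on this count, so there is none to reproduce. The check scores each type of lesion under the rules as written.

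**Rules**
- A: plain sum. Score = (1 if enhancing) + (1 if new or enlarging on T2).
- B: A, less 1 if the lesion is new on T2 and enhancing (the single-lesion rule).
- C: the readers' sentence taken literally. Score = 1 if new or enhancing. This reads the phrase as new or enhancing, which is an assumption.
- D: each distinct active lesion once. Score = 1 if new, enlarging or enhancing.

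| Lesion at week 24 | A | B | C | D |
|---|---|---|---|---|
| New, not enhancing | 1 | 1 | 1 | 1 |
| New, enhancing | 2 | 1 | 1 | 1 |
| Enlarging, not enhancing | 1 | 1 | **0** | 1 |
| Enlarging, enhancing | 2 | **2** | 1 | 1 |
| Unchanged on T2, enhancing | 1 | 1 | 1 | 1 |

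B differs from D in one row only, the enlarging and enhancing lesion. C differs from D in one row only, the enlarging lesion without enhancement. The table does not separate lesions that were already enhancing at baseline.

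**Illustration (assumed counts, not from the documents).** Take one patient with 2 new non-enhancing, 1 new enhancing, 1 enlarging non-enhancing and k enlarging enhancing lesions.

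- A = 2 + 2×1 + 1 + 2k = 5 + 2k
- B = 2 + 1 + 1 + 2k = 4 + 2k
- C = 2 + 1 + k = 3 + k
- D = 2 + 1 + 1 + k = 4 + k

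| k | A | B | C | D |
|---|---|---|---|---|
| 0 | 5 | 4 | 3 | 4 |
| 1 | 7 | 6 | 4 | 5 |
| 2 | 9 | 8 | 5 | 6 |

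The excess from the double count is B − D = k. The shortfall from the literal readers' sentence is D − C = 1, the one enlarging lesion that does not enhance.

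**Scale per arm.** The 45 CIS patients are split equally over three arms: 45 / 3 = 15. With the 30% drop-out allowed for under Sample size, 15 × 0.70 = 10.5, so 10 to 11 remain. One lesion counted wrongly moves an arm mean by 1/15 = 0.07 to 1/10 = 0.10. One patient misclassified as disease-free moves that percentage by 7 to 10 points.

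**The case against.** The strongest reply has four parts.

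- **The total is not an endpoint.** Study endpoints lists T2 lesions and gadolinium-enhancing lesions, the abstract does the same, and the MRI section summarises these two by arm. This stands. A reader might infer that the double count distorts the secondary MRI endpoint or a patient's disease-free status. It does neither. The component counts are unchanged, and a lesion counted twice is activity just as a lesion counted once is.
- **Enhancing is a slip for enlarging.** This is probable, since the word enlarging appears both in the endpoint and in the assessment list. A reader might infer that enlarging lesions will never be recorded and the T2 endpoint cannot be derived. That goes too far, because the assessment list requires them explicitly. What remains is a conflict in the sentence that tells the readers what to determine. Correcting the slip would not remove the double count.
- **Lesions already enhancing at baseline are excluded anyway.** A reader might infer that persistent enhancement enters the total of new lesions, because item 1 is not limited to new enhancement. The text does not clearly support this: the endpoint and the readers' sentence both call for comparison with baseline, and the total is described as new lesions over the 24 weeks. A clarifying phrase would settle it.
- **A journal article leaves overlap rules to the full protocol.** That would excuse silence. Here the article states a sum and an exception, and together they give a count of 2 for one lesion.

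The two problems also come from rival rules and do not both apply to one count: under the literal readers' sentence, the enlarging and enhancing lesion scores 1.

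**Conclusion.** The point holds in a narrow form and is minor. As written, the total counts a T2 lesion that both enlarges and enhances twice, adding exactly one per such lesion. The documents do not give the frequency of these lesions, so the effect on any arm cannot be computed. The excess is confined to the summed total.

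The readers' sentence conflicts with the endpoint and the assessment list. Only if it is followed literally could the T2 endpoint be too low and a patient be wrongly classed as free of disease activity. This rests on the assumption that the reading form would follow that sentence rather than the assessment list, which the documents do not settle.

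The trial is exploratory with an immunologic primary endpoint, and MRI is secondary and done in CIS patients only. No sample size, power or significance figure depends on the count.

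**What to change.** In the MRI section:

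1. Replace the sum with a count of distinct lesions at week 24 that are new on T2, enlarging on T2 or gadolinium-enhancing, each counted once. This extends the single-lesion rule to enlarging lesions.
2. Have the readers' sentence name new T2, enlarging T2 and gadolinium-enhancing lesions, in line with Study endpoints and the assessment list.
3. State that a lesion already enhancing at baseline does not enter a total called new.

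The cost is a few words in the protocol and the same change on the reading form, with the same scans and the same two readers. It should be settled before the scans are read and treatment is unblinded, so that the rule cannot be chosen in the light of the results.
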